## Selected patient enrolment criteria

Eligible patients will be aged 18–80 years at the time of informed consent and have symptomatic PH-HFPEF, e.g. group 2/2.2 of the Dana Point classification [3] and World Health Organization (WHO) class II to IV, defined as:LVEF ≥50 %, diagnosed by echocardiography or left heart catheterization (LHC) within 30 days before randomization,PAPmean ≥25 mm Hg at rest, measured by right heart catheter (RHC) within 12 weeks before randomization,PAWP >15 mm Hg at rest, measured by RHC within 12 weeks before randomization.

The dose regimen of the background treatment must have been stable for >30 days before randomization. Diuretic therapy must have been stable for ≥1 week.

Selected exclusion criteria are listed in Table 1.

**Table 1 Tab1:** Selected exclusion criteria

Cardiac decompensation, either with hospitalization or visit to the emergency department ≤30 days before randomization
Resynchronization therapy
Need of IV diuretics ≤30 days before randomization
Treatment with IV inotropes or IV vasodilators ≤30 days before randomization
Chronic treatment with ERAs, PDE-5 inhibitors or prostanoids ≤30 days before randomization or with nitrates or PDE-5 inhibitors indicated for erectile dysfunction ≤7 days before randomization
Bronchial asthma or COPD with FEV_1_ <60 % of predicted
Restrictive lung disease with TLC <60 % of predicted
Current O_2_ therapy
Clinically relevant hepatic dysfunction indicated by either AST ≥3 times the upper limit of normal or Child-Pugh stage B and C in patients with cirrhosis
Severe renal impairment (glomerular filtration rate <30 ml/min/1.73 m^2^ calculated by the Modification of Diet in Renal Disease formula)
Uncontrolled arterial hypertension (SBP >180 mm Hg or DBP >110 mm Hg)
SBP <100 mm Hg at baseline or clinical signs or symptoms of hypotension
Myocardial disease, such as infiltrative myocardial disease (i. e. amyloidosis, hypertrophic cardiomyopathy)
Severe aortic or mitral stenosis or regurgitation or any valvular stenosis or regurgitation with indications for surgery
Coronary artery disease with angina of Canadian Cardiovascular Society class III or IV or requiring nitrates
Unstable angina or acute myocardial infarction <90 days before randomization
Reperfusion procedure (PCI or coronary artery bypass graft) <90 days prior to randomization or <3 weeks in case of a negative stress test after PCI

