## Statistical considerations

Statistical analyses will be performed using Statistical Analysis Software (SAS®). A randomized subject will be valid for safety analysis if at least one dose of study drug was administered. A subject will be part of the full analysis set (FAS) in accordance to the International Conference on Harmonization (ICH) E9 guideline, if he/she belongs to the safety set, is not violating any major entry criteria and shows any postbaseline efficacy data. A subject will be valid for the per-protocol analysis if the subject belongs to FAS and does not show any major protocol deviations that interfere with the interpretation of efficacy results. All variables will be analyzed descriptively with appropriate statistical methods: categorical variables by frequency tables and continuous variables by sample statistics (e.g. number of non-missing data, mean, standard deviation, minimum, median, quartiles and maximum).

The primary efficacy variable will be submitted to an analysis of covariance (ANCOVA) model including the baseline value as covariate, center, treatment regimen and the interaction term of center by treatment regimen as fixed effects. If the treatment-center interaction is not significant at the 0.2 level, the interaction term will be removed from the model for final analysis. The primary comparison will be a one-sided test at the 2.5 % significance level for the difference in treatment effects between riociguat and placebo.

Continuous secondary endpoints will be analyzed in the same manner as the primary endpoint. The change of WHO class will be dichotomized by defining the groups: “improvement by at least one class”, “no improvement by at least one class” and analyzed using Mantel-Haenszel weights stratified by center. The secondary efficacy variables will be tested in exploratory manner at nominal one-sided significance level of 2.5 %.

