### Determination of sample size

Requiring an 80 % power of the trial to detect a mean difference of at least 0.6 l/min between riociguat and placebo with regard to the primary endpoint and assuming a standard deviation of 1.0 l/min, which is derived from a previous trial (LEPHT), then 45 evaluable subjects are needed in each of the 2 treatment groups. Taking into account a drop-out rate of 20 %, a total of 114 subjects are to be randomized (57 subjects per group).

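### The WHO-class improvement analysis adjusts for center but not for entry WHO class; it is valid, but additive adjustment for class would be a low-cost minor improvement

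*Protocol article*

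**What the plan says.** All of this is in the protocol article.

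- **Primary endpoint** (Statistical considerations): the model is an "analysis of covariance (ANCOVA) model including the baseline value as covariate", with center and treatment as further terms.
- **Continuous secondary endpoints** (same section): "Continuous secondary endpoints will be analyzed in the same manner as the primary endpoint". They are therefore baseline-adjusted too.
- **WHO class** (same section): "The change of WHO class will be dichotomized by defining the groups" improved by one class or more, or not. This binary outcome is then "analyzed using Mantel-Haenszel weights stratified by center". Baseline WHO class is neither a stratum nor a covariate.
- **Population** (Selected patient enrolment criteria): patients enter in "World Health Organization (WHO) class II to IV".
- **Status** (Statistical considerations): "The secondary efficacy variables will be tested in exploratory manner at nominal one-sided significance level of 2.5" %.

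The article gives no distribution of entry class, no expected improvement rates and no number of centers. It describes no stratification of randomization by class.

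**The concern.** The outcome is defined relative to where the patient starts. A class II patient counts as improved only on reaching class I, whereas a class III patient need only reach II and a class IV patient III. Entry class is therefore a natural candidate to predict the outcome, and it is recorded anyway. The plan adjusts every continuous efficacy endpoint for its baseline but leaves baseline out for WHO class, the only categorical secondary variable.

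Two things are at stake, both only if entry class is in fact prognostic. The standard error would be larger than necessary. And in a trial where the arms happen to differ in entry class, part of the observed difference would reflect that imbalance rather than the drug.

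**Working it through.** **1. The plan's own figure.** The article sizes the trial on cardiac output only: difference 0.6 l/min, SD 1.0 l/min, one-sided 2.5%, 80% power. The normal approximation gives 2 × (1.960 + 0.842)² × 1.0² / 0.6² = 43.6, so 44 per group. With the t distribution, 44 gives 79.5% and 45 gives 80.4%, so 45 is right. Then 45 / 0.8 = 56.25, so 57 per group and 114 in total. The stated size reproduces. No power is stated for WHO class.

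**2. How large chance imbalance can be.** With 45 per arm and a share q of patients in class II, the SD of the difference in shares is √(2q(1−q)/45). For q = 0.2, 0.3 and 0.5 (assumed) this is 8.4, 9.7 and 10.5 points. The probability of an imbalance of 10 points or more, in either direction, is 0.24, 0.30 and 0.34.

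**3. What the imbalance does to the estimate.** The approximate shift is the imbalance times the difference in improvement rate between class II and class III/IV. The assumed mix is II/III/IV = 30/60/10%. The simulation used 6000 trials per setting, 5 or 10 centers and a 15-point treatment effect.

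| Placebo rates II/III/IV | III/IV average | Shift per 10-point imbalance | Simulated, center strata |
|---|---|---|---|
| 20/20/20% | 20% | 0.10 × 0 = 0 | about 0 |
| 10/25/25% | 25% | 0.10 × 15 = 1.5 points | 1.6–1.7 points |
| 10/30/40% | (0.6×30 + 0.1×40)/0.7 = 31.4% | 0.10 × 21.4 = 2.1 points | 2.3–2.5 points |
| 5/45/60% | (0.6×45 + 0.1×60)/0.7 = 47.1% | 0.10 × 42.1 = 4.2 points | 3.9–4.3 points |

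The standard error in these settings is about 9 to 10 points. Averaged over all trials, the center-stratified estimate was 0.147 to 0.151 against a true 0.15, so there is no bias.

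**4. Precision.** Assume 45% class II, 55% class III/IV, placebo rates 8% and 30%, and an odds ratio of 2.5.

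- Riociguat rates become 17.9% and 51.7%. Overall rates are 20.1% (placebo) and 36.5% (riociguat).
- Total binomial variance: 0.201 × 0.799 + 0.365 × 0.635 = 0.1606 + 0.2317 = 0.3923.
- Part due to class: 0.45 × 0.55 × (0.220² + 0.339²) = 0.0120 + 0.0284 = 0.0404.
- Ratio without v with class: 0.3923 / (0.3923 − 0.0404) = 1.11.

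With placebo rates of 15% and 25%, the same steps give 0.4004 / (0.4004 − 0.0079) = 1.02. With 20% in both classes the ratio is 1.00. In the simulations of step 3, class strata relative to center strata had an efficiency of 0.98 to 1.05 for null to moderate prognostic strength, and 1.15 to 1.19 in the strongest setting.

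**5. Which adjustment keeps the gain.**

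- *Center fully crossed with class:* efficiency relative to center alone was 0.82 to 1.05. About 5% (5 centers) to 13% (10 centers) of patients fell in one-arm strata and dropped out.
- *Class crossed with pooled centers:* power against center strata was 42.6% v 40.7% at 8/30%, 45.9% v 45.9% at 15/25%, and 47.7% v 48.6% at 20/20%.
- *Additive class and pooled center* (simulated as a linear risk-difference model): power was 43–46% v 38–40% at 8/30%, and 46–48% for both at 15/25% and 20/20%. Null rejection was 1.9–3.7%, against 1.7–3.3% for center strata.

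**The case against.** The strongest reply is that nothing here is wrong. A Mantel-Haenszel comparison stratified by center is a valid analysis of a randomized binary outcome, and it matches the center term in the ANCOVA. The benefit of adding class rests wholly on rates that the article does not give. Supplementary adjusted analyses are often left to an analysis plan, and the endpoint is exploratory. All of that stands and sets the weight of this point. What remains is that the article itself fixes the main analysis of this endpoint and, unlike its continuous endpoints, leaves out a baseline value that is already recorded.

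Three stronger readings are tempting, and the documents support none of them.

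- **The test has inflated type I error.** Among null trials with a class III/IV excess above 10.5 points on riociguat (about 17% of trials), the center-stratified test rejects in roughly 5–7% at assumed rates of 8/30% and 5/35%. That is a selected tail. Imbalance the other way lowers rejection, and the overall rate stays near 2.5%.
- **Some patients cannot improve.** Class I is not enrolled, so every patient can move up a class.
- **Center should be replaced by class.** That would break with the handling of center elsewhere in the plan, and additive adjustment obtains the gain without it.

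**Conclusion.** The point holds as a minor improvement, not as an error. The planned analysis is unbiased and valid over randomizations. If entry class is prognostic, it loses some precision: the variance is about 10% larger at assumed placebo rates of 8% and 30%, and about equal when class is weakly prognostic or not prognostic. Conditional on a 10-point imbalance in entry class, the estimate moves by about 0 to 4 points, less than half its standard error. Class mix, improvement rates, odds ratio and number of centers are all assumptions. The primary conclusion and the 114-patient sample size are untouched.

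**What to change.** In Statistical considerations, change the WHO-class analysis as follows. Analyze improved v not improved with additive adjustment for baseline WHO class (II v III/IV) and center, with small centers pooled by a rule set before unblinding. A logistic model reported as a standardised risk difference would serve. Keep the center-stratified Mantel-Haenszel result as a sensitivity analysis. Do not drop center, and do not fully cross it with class, because the strata become sparse and precision can be lost.

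The cost is a sentence or two before unblinding and slightly more analysis work, with no new data, visits or patients. If class turns out not to be prognostic, there is little or no gain.

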### Change in cardiac output as primary endpoint

The primary objective of the present study is to test the effects of riociguat on the surrogate endpoint CO. While CO is one of the established therapy response markers in PH [3], therapeutic interventions that lead to an increase in CO in left heart disease are under debate. While an increase in CO based on a positive inotropic effect results in elevated left ventricular filling pressures and increased mortality [15], in the LEPHT study [4], which was conducted in heart failure patients, riociguat significantly improved CO in the absence of any significant change in heart rate or SBP compared with placebo. Most importantly, left ventricular filling pressures remained unchanged without excess mortality and clinical benefit was supported by an improvement in quality of life. The mechanisms underlying the observed increase in CO in the LEPHT study are complex. Improvements were not attributable to reflex sympathetic activation elicited by a decrease in SBP. The rise in cardiac function was paralleled by a decrease in PVR and SVR. The potential of direct sGC stimulators in heart failure might go beyond hemodynamic effects and additionally, or even predominantly, rely on non-hemodynamic effects of sGC-derived cGMP signalling in a variety of tissues including cardiac myocytes [16]. Furthermore, preclinical data suggest that sGC stimulation does not increase cyclic adenosine monophosphate (cAMP) production despite significant cGMP increases and may blunt the inotropic response to adrenergic stimulation [17, 18]. In the DILATE-1 study a pronounced effect of riociguat on CO was observed accompanied by size reduction of the right ventricle. These data provide a strong rationale for CO as a primary endpoint in PH-HFPEF patients.

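### Secondary variables get a nominal one-sided 2.5% test with no stated direction; read as a test for benefit, an adverse shift, notably in PAWP, cannot reach nominal significance (low severity, free to repair)

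*Protocol article*

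**What the plan says.** All references are to the protocol article.

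- **Secondary tests.** Under Statistical considerations, the secondary efficacy variables are to be "tested in exploratory manner at nominal one-sided significance level" of 2.5%. No direction is given for any variable.
- **Method.** The same section says: "Continuous secondary endpoints will be analyzed in the same manner as the primary endpoint". That means ANCOVA, with a one-sided 2.5% comparison of riociguat and placebo for the primary variable. WHO class is reduced to improved versus not improved.
- **Description.** The same section also says: "All variables will be analyzed descriptively with appropriate statistical methods".
- **Which variables.** Secondary efficacy variables lists left and right atrial area, right ventricular volume and ejection fraction by CMRI; PVR, SVR, TPG and PAWP by right heart catheter; WHO class; and NT-proBNP.
- **Why filling pressure matters.** Change in cardiac output as primary endpoint calls CO-raising interventions in left heart disease a matter of debate. It says that "an increase in CO based on a positive inotropic effect results in elevated left ventricular filling pressures and increased mortality". It then turns to riociguat in LEPHT: "Most importantly, left ventricular filling pressures remained unchanged without excess mortality".

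**The concern.** A one-sided test needs a direction, and none is written. The context points to benefit: the continuous secondary variables follow the primary analysis, and WHO class is scored only for improvement, so patients who worsen are pooled with those who do not change. On that reading, a fall in PAWP can earn a nominal significance label and an equal rise cannot.

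PAWP is where this asymmetry has most weight. The argument for CO as endpoint leans on filling pressures having stayed unchanged, and that observation comes from LEPHT, a trial in reduced ejection fraction. PAWP is the secondary variable that would check it in the preserved-ejection-fraction population studied here. A test that looks only for a fall cannot flag the finding that would weaken the argument.

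If the direction is instead regarded as open, a different weakness appears. The article does not say which direction counts as favourable for, say, SVR or TPG, and choosing the tail after seeing the data would turn a nominal 2.5% into an effective 5%.

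**Working it through.** **Step 1. Reproduce the plan's own figure.** Inputs from Determination of sample size: difference 0.6 l/min, SD 1.0 l/min, power 80%, 45 evaluable per group, 20% drop-out, 114 randomized. The one-sided 2.5% level is from Statistical considerations.

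- Normal approximation: n = 2 × (1.960 + 0.842)² / 0.6² = 43.6, so 44 per group.
- Exact (noncentral t): power 79.5% at 44 and 80.4% at 45 per group, so 45 are needed, as stated.
- Drop-out: 45 / 0.8 = 56.25, rounded up to 57 per group, 114 in total, as stated.

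**Step 2. Compare the thresholds on the benefit side.** One-sided 2.5% and two-sided 5% both use the 97.5% point: z = 1.960, or t = 1.987 with 2 × 45 − 2 = 88 degrees of freedom. Declaring benefit is equally hard under either rule, so power for benefit and sample size do not change.

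**Step 3. Compare the rules when the true shift is adverse.** For a standardised adverse shift d, the noncentrality is d × √(n/2) = d × √22.5 = d × 4.743. The one-sided benefit test rejects only if t falls beyond 1.987 on the favourable side. The two-sided test also rejects beyond 1.987 on the adverse side. With n = 45 per group:

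| Assumed adverse shift | Noncentrality | One-sided benefit test rejects | Two-sided 5% test flags harm |
|---|---|---|---|
| 0.3 SD | 1.42 | 0.04% | 29% |
| 0.4 SD | 1.90 | 0.006% | 47% |
| 0.5 SD | 2.37 | <0.001% | 65% |
| 0.6 SD | 2.85 | about 0.0001% | 80% |
| 0.8 SD | 3.79 | about 0% | 96% |

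The few one-sided rejections in the third column would be false signals of benefit, not detections of harm.

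**Step 4. Smallest observed adverse difference that a two-sided test would flag.** 1.987 × √(2/45) = 1.987 × 0.211 = 0.42 SD.

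**Limits.** The article gives no SD or relevant difference for any secondary variable, so the shifts are assumptions; 0.6 SD is simply the standardised effect used for CO. The calculation is an unadjusted two-sample t test. The planned ANCOVA, with baseline and centre, would alter the exact percentages but not the contrast.

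**The case against.** The strongest reply is that little is lost in practice.

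- **Exploratory status.** The tests are nominal and no decision rule hangs on them, so nothing is confirmed in either direction. This stands and sets the severity. It also removes any reason to restrict the direction.
- **Harm stays visible.** The ANCOVA difference carries its sign and every variable is described. A reader might infer that the trial could not detect or report a rise in PAWP. The article does not support that; only the nominal significance label is lost.
- **The rationale is narrower than it may seem.** A reader might infer that the article names higher filling pressure as the key risk of raising CO. It ties that risk to a positive inotropic effect and cites LEPHT as evidence against it for riociguat. The harms it names are filling pressure and mortality, not NT-proBNP, TPG or chamber size. The argument from the rationale therefore reaches PAWP and no other secondary variable.
- **Harm is looked for elsewhere.** All-cause mortality, a cardiovascular composite and clinical worsening are exploratory variables, outside the sentence on secondary tests, and a safety set is defined. This stands.
- **Confidence intervals.** A journal article may leave these to the analysis plan, so their absence here is no fault. If the analysis plan provides two-sided intervals, most of the practical problem disappears.
- **The power contrast is built in.** A test with one tail hardly ever rejects in the other. True; the figures show the size of the asymmetry, not the chance of seeing harm.

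What survives is that the one-sided level is a written choice, its direction is not, and nothing else in the article supplies a two-sided test for the secondary variables.

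**Conclusion.** The point holds as a low-severity improvement. The article fixes a nominal one-sided 2.5% test for all secondary variables and leaves its direction unstated. If the direction is benefit, which is an inference though a natural one, an adverse shift cannot reach nominal significance. At 45 per group and an assumed 0.5 SD, the contrast is less than 0.001% against 65%. The consequence is clearest for PAWP, because unchanged filling pressure is part of the case for CO as endpoint. The primary test, its type I error and the sample size of 114 are unaffected.

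**What to change.** Replace the sentence on secondary tests in Statistical considerations with wording such as: *Each secondary efficacy variable is tested in exploratory fashion, two-sided at a nominal 5% level, and its treatment difference is reported with a two-sided 95% confidence interval.* The primary one-sided 2.5% test can stay.

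The cost is one sentence in the protocol and the matching line in the analysis plan. No patients are added and the threshold for benefit does not move. With no true effect, the chance of a nominal flag per variable rises from 2.5% to 5%. The added 2.5% consists of false flags in the adverse direction, while the rate of false signals of benefit stays at 2.5%.

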### Determination of sample size

Requiring an 80 % power of the trial to detect a mean difference of at least 0.6 l/min between riociguat and placebo with regard to the primary endpoint and assuming a standard deviation of 1.0 l/min, which is derived from a previous trial (LEPHT), then 45 evaluable subjects are needed in each of the 2 treatment groups. Taking into account a drop-out rate of 20 %, a total of 114 subjects are to be randomized (57 subjects per group).

## Discussion

The DYNAMIC study is the first randomized, double-blind, placebo-controlled, multi-center trial testing the effects of an oral soluble guanylate cyclase (sGC) stimulator targeting PH due to HFPEF. The results will potentially be of great clinical relevance given the high prevalence of PH among patients with HFPEF and its influence on morbidity and mortality.

### Pulmonary vasodilators in heart failure with preserved ejection fraction

Pulmonary vasodilators have previously been studied in only few clinical trials, which have yielded conflicting results. In a placebo-controlled, single center clinical study in PH-HFPEF patients, the phosphodiesterase-5 inhibitor sildenafil lowered pulmonary artery pressure and improved right ventricular function [8]. By contrast, sildenafil failed to improve endpoints in a cohort of HFPEF patients without significant PH [9]. In the RELAX trial [9] peak O_2_ consumption was not changed in the treatment arm as compared with placebo. Secondary endpoints including change in 6 min walking distance, composite clinical status score and change in quality of life at 24 weeks were also missed. Moreover, subgroup analysis showed no improvement in peak O_2_ consumption in patients with higher pulmonary artery systolic pressure where the median was 41 mm Hg (range 32–51 mm Hg) in the treatment group.

Currently, two additional multicenter, placebo-controlled clinical trials testing the effects of pulmonary vasodilators in HFPEF are underway. The SOCRATES PRESERVED program was designed to study the effects of the novel once-daily oral sGC stimulator vericiguat (BAY 1021189) in a phase II dose-finding study among patients with HFPEF stabilized after hospitalization or i. v. diuretic therapy for worsening of chronic heart failure [10]. Although the DYNAMIC study follows a similar study rationale that is based on systemic vasoreactivity and potential cardiac effects of the sGC stimulator, main differences with respect to SOCRATES PRESERVED are the patient population under investigation (HFPEF versus PH-HFPEF) and main study endpoints (change in NT-proBNP and left atrial volume at 12 weeks versus invasively measured CO at 26 weeks).

The MELODY study, which has recently been rolled out, focuses on the effects of macitentan, a novel dual endothelin receptor blocker versus placebo in a rare subpopulation of PH-HFPEF patients, which are characterized by elevated pulmonary diastolic pressure gradients indicative of true pulmonary vascular remodelling on top of elevated left-sided filling pressures; however, there is cumulating evidence that the use of riociguat in patients with PH associated with heart failure is most effective in the subgroup with a PVR <240 dyn ×s ×cm^−5^ [11]. Given the uncertainties regarding the optimal target population, i. e. pure postcapillary versus combined precapillary and postcapillary PH, the current protocol will be open for a broad range of hemodynamic profiles of patients fulfilling the diagnostic criteria of postcapillary PH.

